### Objectives:

- (1) Primary objective: investigating whether the modulation of the ACC activation level through fMRI-neurofeedback training reduces ADHD symptoms and improves cognitive functioning.
- (2) Secondary objective: investigating if abnormal activation levels of the ACC in ADHD patients play a causal role in ADHD pathophysiology.

**Study design:** Randomized controlled treatment study with blinding of participants.

**Study population:** 20 subjects with ADHD (age > 18, IQ > 100).

**Intervention:** 10 subjects with ADHD receive 6 sessions with fMRI-neurofeedback from the dorsal anterior cingulate cortex, and 10 subjects with ADHD receive 6 sessions with fMRI-neurofeedback from a control region.

**Main study parameter:** ADHD-DSM-IV rating scale (rated blindly).

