### 3. Study Design

This study is a randomized controlled trial (RTC) with blinding of the participants and blinding of all raters. ADHD adults will be blindly allocated to one of the following two groups by a restricted randomization technique (see recruitment section):

1. fMRI-neurofeedback training, feedback from dorsal anterior cingulate cortex (n=10)
2. fMRI-neurofeedback training, feedback from control brain region (n=10)

Each group will receive the same screening, pre- and post-assessment and 6 fMRI-neurofeedback training sessions. The duration of each fMRI-neurofeedback training session will be approximately 75 minutes. The frequency will be weekly sessions. The duration of the experiment for each participant from the selection until the last session will be approximately 9 weeks.

The control group will receive exactly the same as the fMRI-neurofeedback group, except for the feedback. The control group will receive feedback from a control brain region, which will be selected such that it is activated by different tasks than the dorsal anterior cingulate cortex. This selection will be made based on literature research, previous data, and data from an ongoing pilot experiment.

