## 5. Treatment of Subjects

The fMRI-neurofeedback training will proceed as follows. Before the training the subjects will be suggested a set of cognitive strategies that they may use during the neurofeedback training (the same set of strategies in both groups). These cognitive strategies will be derived from research on which mental tasks activate the neurofeedback and the control region. Towards the patients it will be stressed that they are also always free to choose any other strategy that seems to work, and that they should be guided by the feedback in the selection of their strategy.

At the beginning of each scanner session patients will be given ear plugs to protect them against the scanner noise. Additionally, they will be given customized headphones which enable them to communicate with the researchers at any point of time of the scanning session. Also, they will receive an alarm button, which they can press at any point of time if they wish to interrupt the scanning session immediately. The participants will be moved into the fMRI scanner lying on their back with their head fixated by small foam cushions to prevent excessive head movement. In the scanner they will always have the projection of a full computer display visible in a mirror, which is mounted directly in front of their eyes. This display will later be used to present them with the feedback regarding their own brain activation (see figure below for setup).

The training scan session will then start with the 10 minute multisource interference task during which the participants will have to identify a target number 1, 2, or 3 in an adapted Flanker task by button presses. The brain activation measured during this interference task will be used to functionally localize the feedback target region immediately after this functional scan. The localization of the feedback target region will be done by researchers with ample experience in localizing feedback target regions in general, as well as with localizing the ACC based on the interference task proposed in this study. The necessary analysis will be performed during the following 8 minute anatomical scan. The subject will not have to spend any additional time in the scanner, as the anatomical scan is needed for co-registration of the data in any case. During the anatomical scan the patient will be told to relax, and watch a short silent video that will be presented on the display to divert them from the scanner environment.

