### **Withdrawal of individual subjects**

Subjects can leave the study at any time for any reason if they wish to do so without any consequences. The principal investigator can also withdraw a subject if:

- The investigator believes that for safety reasons (e.g. in the presence of adverse events) it is in the best interest of the subject to stop treatment.
- The subject is unwilling to cooperate for reasons not related to the trial treatment.

An intercurrent illness emerges of which the severity, duration, or required treatment violated the conditions of the trial.

Subjects withdrawn from the study for a medical reason will be followed until the adverse events have been resolved.

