## 8. Statistical Analysis

**Related to primary objective (1):** Investigate whether fMRI-neurofeedback training reduces ADHD symptoms.

For the ADHD symptom score, the sustained attention measures, the working memory measures, and the fMRI resting state anterior cingulate cortex connectivity several independent 2 x 2- way ANCOVAs (one per outcome measure) will be conducted (two-tailed, significance level is set at 5%) with session (pre-vs. post-treatment) as within-subjects factor, group (fMRI-neurofeedback vs. control neurofeedback) as between-subjects factor, and age, sex and IQ as covariates.

For the cognitive interference measures, and the fMRI anterior cingulate cortex activation level/ connectivity during MSIT several independent 6 x 2- way ANCOVA (one per outcome measure) will be conducted (two-tailed, significance level is set at 5%) with session (number of training session) as within-subjects factor, group (fMRI-neurofeedback vs. control neurofeedback) as between-subjects factor, and age, sex and IQ as covariates.

The influence of current state of motivation on training success will be calculated by computing non-parametric Spearman's rank correlations within each individual patient.

The mental strategies used will be scored and their influence on training success will be evaluated by computing non-parametric Spearman's rank correlations within each individual patient.

**Related to secondary objective (2):** Investigate if the abnormal activation levels in ADHD patients play a causal role in ADHD pathophysiology.

To estimate the influence of the neurofeedback training on the symptoms a measure of change in activation level during the neurofeedback training/ the transfer blocks at the end of the training will be developed. This measure (sessions x subjects) will be correlated with the performance on the MSIT task in the subsequent session within and across the two groups (fMRI-neurofeedback and control neurofeedback).

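### The MSIT outcomes are assigned a 6 x 2 repeated-measures ANCOVA, whose classical form uses only patients with all six sessions; a mixed model would keep every session collected

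*Protocol*

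**What the plan says.** The protocol plans 20 patients, 10 per arm. Section 3 (Study Design) states: "Each group will receive the same screening, pre- and post-assessment and 6 fMRI-neurofeedback training sessions". Sessions are weekly.

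Section 8 (Statistical Analysis) uses two models. The ADHD symptom score, sustained attention, working memory and resting-state connectivity are analysed in 2 x 2 pre/post ANCOVAs. For cognitive interference and for anterior cingulate activation or connectivity during the MSIT, "several independent 6 x 2- way ANCOVA (one per outcome measure) will be conducted", "with session (number of training session) as within-subjects factor", with group as the between-subjects factor "and age, sex and IQ as covariates". These six-session outcomes are listed under the primary objective, but the Summary names the ADHD-DSM-IV rating scale as the main study parameter.

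The protocol allows for incomplete participation. Section 6 (Withdrawal of individual subjects) states: "Subjects can leave the study at any time for any reason if they wish to do so without any consequences". It also lets the principal investigator withdraw a patient for safety, non-cooperation or intercurrent illness. Section 5 (Treatment of Subjects) gives each patient an alarm button, "which they can press at any point of time if they wish to interrupt the scanning session immediately". Sections 5 and 6 both place the MSIT first in each training scan, before the anatomical scan and the neurofeedback blocks.

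**The concern.** A repeated-measures ANCOVA with a six-level within-subjects factor, run in the classical way, works on one row per patient with six filled cells. One empty cell removes the row. A patient who leaves after session 4 has four MSIT records and a patient with one failed run has five, yet neither is used.

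With 20 patients there is little reserve. Each discarded record comes from a visit of about 75 minutes that the patient completed. The analysis also becomes a comparison of patients selected after randomisation, namely those with every MSIT run usable. The objection is to the model that Section 8 names. It is not that the protocol lacks a missing-data section, which a separate analysis plan could supply.

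**Working it through.** The protocol gives no expected loss, dropout, power or effect size, so there is no figure to reproduce. What follows is a range under stated assumptions.

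**Inputs from the protocol:** N = 20 (10 per arm), six sessions, three covariates. Planned patient-sessions: 20 × 6 = 120.

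**Assumption:** each session's MSIT record is lost with probability p, independently across sessions and patients.

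**Formulas:**
- Complete patients: 20 × (1 − p)^6
- Records observed: 120 × (1 − p)
- Records used by complete-case analysis: 120 × (1 − p)^6
- Share of observed records discarded: 1 − (1 − p)^5

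| p | (1 − p)^6 | Complete patients of 20 | Records observed | Records used | Observed records discarded |
|---|---|---|---|---|---|
| 1% | 0.941 | 18.8 | 118.8 | 113.0 | 5% |
| 2% | 0.886 | 17.7 | 117.6 | 106.3 | 10% |
| 3% | 0.833 | 16.7 | 116.4 | 100.0 | 14% |
| 5% | 0.735 | 14.7 | 114.0 | 88.2 | 23% |
| 10% | 0.531 | 10.6 | 108.0 | 63.8 | 41% |

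**Adding withdrawal.** If a further 10% of patients are assumed to stop early, 20 × 0.9 × (1 − p)^6 leaves 15.9, 13.2 and 9.6 complete patients at p = 2%, 5% and 10%.

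**Relaxing independence.** Withdrawal and recurrent poor scans cluster within patients. Take a beta-binomial loss with an assumed within-patient correlation of 0.3, so that the two beta parameters sum to 1/0.3 − 1 = 2.333. The probability of six complete sessions is the product over i = 0 to 5 of [2.333(1 − p) + i] / [2.333 + i]. This is 0.843 at p = 5% and 0.706 at p = 10%, or 16.9 and 14.1 complete patients instead of 14.7 and 10.6.

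**Precision.** Missingness patterns were simulated for 10 v 10 patients with compound symmetry, correlation 0.6, data missing completely at random and no covariates. The generalised least squares standard error of the group difference in linear session trend was compared between complete cases and all observed records. The ratios were 1.06, 1.15 and 1.35 at p = 2%, 5% and 10%. Squared, these give variance ratios of about 1.12, 1.32 and 1.82. A separate simulation with correlations of 0.3 to 0.6 gave 1.34 and 1.84 at 5% and 10%. The linear trend is one summary of the session-by-group effect. Section 8 specifies a six-level factor, so these ratios show the order of the loss rather than the exact loss for the planned test.

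**Degrees of freedom.** The between-group test has N − 5 error degrees of freedom (intercept, group, three covariates): 15 at N = 20, 10 at N = 15 and 5 at N = 10. The univariate session-by-group test has 5(N − 5): 75, 50 and 25, before any sphericity correction. A shortage of error degrees of freedom therefore concerns mainly the between-group test.

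**The case against.** The strongest reply is that the protocol nowhere says incomplete records will be dropped. That is correct: deletion is inferred from the classical form of the named model, and an analysis plan could add imputation. The point that remains is narrower. Section 8 commits to a model that needs complete rows when one that does not is readily available.

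Four stronger readings are tempting, and the documents do not support them.

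- **That a large part of the 20 patients will be lost.** No loss rate is given. At 1% to 2% only about one or two patients go. Clustering leaves more complete patients than the independent calculation. The session factor is the number of the training session, not the calendar week, so a postponed visit need not leave a gap; the protocol neither provides for nor rules out postponement. Patients uncomfortable in the practice scan are also excluded before training starts.
- **That any interrupted scan costs the session.** The MSIT comes first, so a stop during the anatomical scan or the training loses no MSIT data. Head movement may spoil an imaging run, but it does not remove the behavioural interference score, and the protocol describes precautions against movement rather than expected losses.
- **That the comparison is biased because loss differs by arm.** This is possible but not documented. Participants are blinded, both arms are offered the same strategies, and the procedures differ only in the region that supplies the feedback.
- **That the trial's main result is at risk.** The ADHD rating scale is analysed pre/post, and a missed training session does not remove it.

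A mixed model also has limits. It recovers nothing for a patient without any training session, and it can be biased if loss depends on unobserved values.

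**Conclusion.** The point holds for the MSIT outcomes only. The named model, in its classical form, discards every session of any patient with one missing or unusable MSIT record. The cost depends on a loss rate that has to be assumed: slight at 1% to 2%, about a quarter of patients at 5% under independence, and nearly half at 10%. At 5% and 10% the variance of the group difference in session trend is about 1.3 and 1.8 times what the collected data would allow. These figures assume independent losses and compound symmetry; within-patient clustering leaves more complete patients. The change is worth making because it costs little and these outcomes serve the primary objective. It is not a defect in the analysis of the main study parameter.

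**What to change.** In Section 8, replace the 6 x 2 ANCOVA sentence with a linear mixed model, one per MSIT outcome, on all available session records of every randomised patient with at least one session, in the allocated arm. Specify:

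- fixed effects for session (six levels), group, session x group, age, sex and IQ;
- one prespecified, parsimonious within-patient covariance, for example a patient random intercept with AR(1) residuals. An unstructured 6 x 6 matrix has 6 × 7 / 2 = 21 parameters, too many for 20 patients;
- Kenward-Roger degrees of freedom, keeping the two-sided 5% level.

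Sessions before a withdrawal, and those on either side of a lost run, then stay in the analysis.

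The cost is a change of wording: no added patients, visits or measurements, and standard software. The small downside is that a covariance structure must be fixed in advance and the model assumes data are missing at random, which is generally weaker than what a complete-case analysis requires. If no session is lost, little is given up.

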## 2. Objectives

The primary objective of this study will be to critically evaluate if the fMRI-neurofeedback training is successful in reducing ADHD symptoms and improving cognitive functioning. Thus, the first goal is to show that ADHD patients are able to voluntarily modulate their individual anterior cingulate cortex activation level. Secondly, it has to be demonstrated that this modulation has a specific influence on ADHD symptoms and the performance during cognitive tasks. Finally, it has to be critically evaluated which outcome measures are positively modulated, and which are the moderating factors for treatment success. All the cognitive tasks that have been included in the design are also possible moderating factors.

The secondary objective of this study is further enhancing the understanding of the pathophysiology of ADHD. Neurofeedback studies in general are seen as an excellent tool for investigating the causal influence of abnormal brain activation levels. As the regional brain activation level is manipulated in a neurofeedback experiment, the ADHD symptoms and cognitive functioning become the outcome measure. If one would succeed in influencing behavior through manipulating brain activation patterns, this would be strong evidence for a causal role of the abnormal activation levels of the anterior cingulate cortex in the pathophysiology of ADHD.

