- The fMRI session will proceed as follows. Subjects will be carefully instructed to remove all metal objects before entering the MRI scanner. To restrict head movements and to limit motion artefacts, the participant's head will be fixed by foam cushions and ear clamps positioned behind the neck and around the head. Participants will also be reminded to keep their head as still as possible. Headphones customized for MRI experiments will be inserted into the head coil and will provide isolation from scanner noise. These headphones will also be used to present instructions to the participants. To accustom subjects to the scanner noise the anatomical scan will be performed first.
- A high-resolution anatomical MRI scan will be acquired that is optimized for volumetric measurement of individual brain areas and of gray and white matter volumes and that can serve as anatomical reference for the functional scans. Subjects are told to relax and lie still during the anatomical scan.

- Second the resting-state scan will be performed. Resting-state fMRI measures fluctuations in the Blood-Oxygen-Level-Dependent (BOLD) signal in gray matter brain areas while the subject is at rest (not performing a task). Participants will be instructed to relax and remain still with eyes open for 8 minutes in the fMRI scanner.

During the second week the first **fMRI-neurofeedback training** session (~75 minutes) will take place. At the beginning of the session subjects are asked to fill in a short questionnaire on their current state of motivation regarding the training. Previous neurofeedback studies have shown that state of motivation is an important predictor of training success (Hammer et al., 2012; Nijboer, Birbaumer, & Kubler, 2010). Current state of motivation will be measured using an adapted version of Questionnaire for Current Motivation (QCM) (Nijboer, Birbaumer, & Kubler, 2010; Rheinberg, Vollmeyer, & Burns, 2001).

- The QCM (~10 minutes) consists of 18 short statements which have to be rated to which extent they apply on a 7-point Likert-type scale. Four factors of motivation (mastery confidence, incompetence fear, interest, and challenge) can be extracted from these 18 items.

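### Motivation and strategy effects are fixed as a separate six-session Spearman correlation within each patient, with no group-level estimate stated

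*Protocol*

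**What the plan says.** Protocol Section 8 gives the motivation analysis in one sentence: "The influence of current state of motivation on training success will be calculated by computing non-parametric" "Spearman's rank correlations within each individual patient". The next sentence treats strategies alike: "The mental strategies used will be scored and their influence on training success will be evaluated by computing non-parametric" Spearman correlations, again within the individual patient. Neither sentence gives a significance level, a p-value method, a definition of training success or a step that combines patients.

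The number of pairs follows from the design. Section 3: "Each group will receive the same screening, pre- and post-assessment and 6 fMRI-neurofeedback training sessions". Section 6 (Overview Performed Measurements) places the motivation questionnaire (QCM) at the start of training: "At the beginning of the session subjects are asked to fill in a short questionnaire on their current state of motivation". Strategies are recorded by questionnaire after each training, and the Summary Measurements list both as training-session measures. On the QCM the protocol adds: "Four factors of motivation (mastery confidence, incompetence fear, interest, and challenge) can be extracted from these 18 items".

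Section 6 justifies collecting the QCM by citing earlier neurofeedback studies in which motivation predicted training success. Section 2 asks, among other things, "which are the moderating factors for treatment success".

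**The concern.** The stated unit of analysis does not fit the question. The QCM is collected because motivation is expected to predict how well training works. That question has two parts: do more motivated patients train better, and does a patient train better in sessions where motivation is higher? A within-patient rank correlation removes the first part by construction. It addresses the second with six points at a time and leaves up to 20 separate coefficients per score.

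Time is also left out. Training is meant to raise skill over the sessions. If motivation also moves over the sessions, the two series will correlate within a patient even when neither affects the other.

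At stake is whether the motivation and strategy data, collected from every patient at every session, yield an interpretable statement about the trained population.

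**Working it through.** The protocol gives no power or critical value for these correlations, so there is no stated figure to reproduce.

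**Inputs**
- Patients: 20, 10 per group (Summary; Section 3).
- Pairs per coefficient: at most 6, one per training session (Sections 3 and 6).
- Motivation scores: one overall score, or up to four QCM factors (Section 6).
- Two-sided 5%: assumed. Section 8 attaches it to the ANCOVAs only.

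**1. Critical value.** For n = 6 without ties, rho = 1 - 6 x sum(d^2)/210. Enumerating all 6! = 720 rank orders:
- |rho| >= 0.886 occurs in 24 orders: p = 24/720 = 0.033.
- |rho| >= 0.829, the next attainable value, occurs in 42: p = 42/720 = 0.058.

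Under the t approximation, t = rho x sqrt(4/(1 - rho^2)), the cut-off is 0.811. The attainable 0.829 then has nominal p = 0.041, although its exact error rate is 0.058. If one session is missing (n = 5), the exact test needs |rho| = 1.0, because 0.9 gives 10/120 = 0.083.

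**2. Power for one patient.** Simulated with bivariate normal data and independent sessions:

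| True correlation | Exact test | t approximation |
|---|---|---|
| 0.3 | 5% | 9% |
| 0.5 | 10% | 16% |
| 0.7 | 21% | 31% |
| 0.8 | 31% | 44% |

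**3. Chance findings, exact test.** One motivation score: 20 x 0.0333 = 0.7 expected, with probability 1 - (1 - 0.0333)^20 = 49% of at least one. Four factors: 80 x 0.0333 = 2.7 expected, with probability 93% of at least one if the tests are treated as independent. Strategy scores would add to these counts.

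**4. What the same data can support at group level, true correlation 0.3.**
- One-sample t-test on the 20 per-patient coefficients: about 67-69% power by simulation, assuming the same correlation in every patient.
- Pooled within-patient slope: 120 records - 20 patient means - 5 session contrasts - 1 slope = 94 degrees of freedom. By Fisher's z with an effective 92, atanh(0.3) x sqrt(92) = 0.3095 x 9.59 = 2.97, and power = Phi(2.97 - 1.96) = 84%. This assumes one slope common to all patients.

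**5. Session trend (illustration only).** Suppose motivation and success both drift linearly over the six sessions, with the spread of the drift equal to the residual SD and no link between them. The average six-point Spearman coefficient is then about 0.53, and about 13% of patients pass the exact threshold. The protocol gives no figure for drift, so the size is hypothetical. The mechanism needs only a shared trend.

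**The case against.** Section 8 speaks of calculating and evaluating an influence and sets no test for these coefficients. A reader might infer that significance is possible only at 0.886; that rests on the exact test and an assumed 5% level, and 0.829 passes under the t approximation. This stands. The threshold and power figures are therefore conditional.

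A reader might also infer that the plan cannot answer the question for the group. The documents do not support that. Per-patient coefficients are valid first-stage summaries, and a second-stage test could sit in an analysis plan that is not shown. It would have about 67-69% power at 0.3, so setting single-patient power against pooled power is not by itself a fair contrast. This stands too. However, such a step would recover only the within-patient question, and unadjusted coefficients would carry any session trend with them. In its secondary-objective paragraph Section 8 does describe a correlation taken over groups, so the patient-level unit here reads as a choice.

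Four further inferences go too far:
- **Eighty tests are planned.** The factors can be extracted, but Section 8 does not say that all four are analysed.
- **Strategies cannot be ranked.** They are to be scored, and the scoring is not shown.
- **The correlation is undefined because success means symptom change.** Section 8 does not say this, and session-level measures exist.
- **A primary-objective analysis fails.** The moderators that Section 2 names are the cognitive tasks. Motivation and strategies are not named there, and the summary objectives mention no moderators.

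**Conclusion.** The point holds in a limited form. Section 8 fixes a method and unit of analysis that give at most six pairs per coefficient, state no group estimate, discard between-patient differences in motivation and ignore trend over sessions. That goes beyond detail left for later, because the method is positively stated.

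Read patient by patient at an assumed two-sided 5%, the coefficients are close to uninformative at moderate correlations, whichever p-value method is used. The 0.7 to 2.7 expected chance hits span one motivation score to four. The power figures rest on normal data, independent sessions, no ties and complete attendance; one missed session makes the exact test harsher still.

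The consequence is confined to the predictor analyses. The symptom and cognitive comparisons between groups are unaffected.

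**What to change.** Amend the two sentences in Section 8.

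1. Define training success per session as signal change in the region the patient was trained on, for example in the transfer blocks. Standardise it within region, or include a group interaction. Dorsal anterior cingulate signal should not serve for both groups, because controls receive feedback from another region.
2. For each motivation score, fit one mixed model over all 20 x 6 session records, with patient-mean-centred motivation, patient-mean motivation, session and group as fixed effects and a patient random intercept. Add a random slope, or use cluster-robust or small-sample standard errors, so that differing slopes do not make the intervals too narrow.
3. Report within-patient and between-patient slopes with 95% confidence intervals, noting that the between-patient slope rests on only 20 patients.
4. State whether one motivation score or four factors will be analysed.
5. Enter the strategy score in the same way, as ordinal or categorical according to how it is scored.
6. Keep the per-patient Spearman coefficients as description.

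The cost is a wording change, slightly more analysis work and reliance on linearity and, for the quoted power, a common slope. No new data or visits are needed.

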### Summary objectives

- (1) Primary objective: investigating whether the modulation of the ACC activation level through fMRI-neurofeedback training reduces ADHD symptoms and improves cognitive functioning.
- (2) Secondary objective: investigating if abnormal activation levels of the ACC in ADHD patients play a causal role in ADHD pathophysiology.

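### The causal-role correlation uses repeated session-by-patient records with no patient or session term, so its error rate is uncontrolled, and it names symptoms as its aim but uses MSIT performance.

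*Protocol*

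**What the plan says.** The secondary objective is "investigating if abnormal activation levels of the ACC in ADHD patients play a causal role in ADHD pathophysiology" (Section 2, summary of objectives). Section 8 gives one analysis under it. The sentence opens "To estimate the influence of the neurofeedback training on the symptoms a measure of change in activation level", taken from the training or transfer blocks and still to be developed. It continues: "This measure (sessions x subjects) will be correlated with the performance on the MSIT task in the subsequent session". This is to be done for each arm separately and for both arms together.

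The two correlations just above it in Section 8, for motivation and mental strategies, are handled differently. They are to be done by "computing non-parametric Spearman's rank correlations within each individual patient". The causal-role correlation is specified by group, not by patient.

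Section 2 also says that "the first goal is to show that ADHD patients are able to voluntarily modulate their individual anterior cingulate cortex activation level". The 6 x 2 models in Section 8 analyse ACC activation during the MSIT, not during feedback or transfer blocks.

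**The concern.** Each patient contributes several records to this correlation. Two mechanisms can produce a correlation when regulation and performance are unrelated:

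- **Clustering.** If patients differ stably on both variables, chance alignment of those differences is repeated in every session. The effective sample size is then smaller than the record count.
- **Shared trend.** Patients train weekly and are encouraged to practise strategies at home, while the MSIT is repeated at every session. If both variables drift with session number, they correlate through time alone.

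There is also a mismatch of target. The declared aim is influence on symptoms, but the variable is MSIT performance, which Section 6 (Summary Measurements) lists as cognitive interference. The ADHD score is listed only as a pre-post measure, so it could not enter a session-by-session correlation.

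At stake is the one analysis assigned to the causal-role objective. A nominally significant result could reflect stable patient differences or practice, and it would not by itself concern symptoms.

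**Working it through.** The Protocol states no error rate or power for this analysis, so there is no figure to reproduce.

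**Inputs from the Protocol**
- Patients: 10 per arm, 20 in total, 6 sessions each (Summary, Section 3).
- Pairs: the MSIT opens every session (Section 6), so training in sessions 1-5 pairs with the MSIT in sessions 2-6. That gives 5 pairs per patient and 20 x 5 = 100 records. Pairing session 6 with the post-training MSIT gives 20 x 6 = 120.
- Level: 5% two-sided. This is stated for the ANCOVAs only and is assumed to apply here.

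**Assumptions, because the Protocol gives no values**
- Between-patient stability (ICC) of each variable: 0 to 0.8.
- A linear trend common to all patients in both variables: 0, 0.5 or 1 SD from first to last session.

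**Closed form, no trend.** With k pairs per patient, the variance of the pooled correlation is inflated by

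D = 1 + (k - 1) x ICCx x ICCy,

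and the false-positive rate is about 2 x [1 - Φ(1.96/√D)]. For k = 5 and both ICCs 0.5, D = 1 + 4 x 0.25 = 2.00, 1.96/√2.00 = 1.39, and the rate is 16.6%.

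**Simulation.** Pearson test on 100 records, no true association, 5,000 trials per setting:

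| ICC (both variables) | D | Closed form, no trend | Simulated, no trend | Trend 0.5 SD | Trend 1 SD |
|---|---|---|---|---|---|
| 0 | 1.00 | 5.0% | 4.5% | 6.1% | 19.3% |
| 0.2 | 1.16 | 6.9% | 6.7% | 7.6% | 21.4% |
| 0.3 | 1.36 | 9.3% | 9.0% | 10.3% | 23.3% |
| 0.5 | 2.00 | 16.6% | 15.3% | 16.2% | 28.5% |
| 0.7 | 2.96 | 25.5% | 26.9% | 25.5% | 34.3% |

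**Low stability of activation change.** D depends on the product of the ICCs, so one low value protects the test. Simulated rates (activation ICC / MSIT ICC) are 5.2% at 0/0.7, 6.8% at 0.1/0.5 and 7.9% at 0.1/0.7. The last becomes 8.8% with a 0.5 SD trend.

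**Variants, no trend.** Within one arm (10 x 5 = 50 records) the rates are 8.8%, 15.6% and 25.7% at ICC 0.3, 0.5 and 0.7. With 6 pairs per patient (20 patients) they are 10.1%, 18.6% and 29.1%.

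**Which adjustment works**
- Removing patient means alone is not enough under a common trend. At ICC 0.5 with a 1 SD trend the rate is 59.2%.
- Removing patient and session means, with (patients - 1) x (pairs - 1) - 1 degrees of freedom, gives 4.4-5.7% in every setting run.
- If each patient has an own slope (SD 1, independent between the two variables), that two-way centring still gives about 7%.

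**The case against.** **The text does not state independence.** It names no coefficient and no record count, the sessions-by-subjects label shows that the authors saw the repeated structure, and a separate analysis plan might supply the method. It stands that independence is the plain reading and not a written rule. But the Protocol itself fixes the unit, the pairing and the grouping, and it asks for within-patient analysis in the neighbouring correlations but not here. That is more than a detail left for later.

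**The inflation rests on assumed inputs.** This stands. A reader might infer that false positives run at several times 5% whatever the data look like. The documents do not support that: the activation variable is a change measure, which may carry little stable between-patient variation, and without a strong trend the rate is then 5-8%.

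**The control arm might be measured on another region.** A reader might infer this because the arms receive feedback from different regions and Section 8 says only activation level. It is no more than a possibility. The objective names the ACC, and Section 6 lists ACC activation during neurofeedback without restriction by arm. The wording needs one clarifying phrase.

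**The MSIT is a legitimate outcome.** Also true. Section 2 makes both symptoms and cognitive functioning outcomes for this objective. The fault is that the analysis is said to address symptoms.

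**The causal argument does not rest on this correlation alone.** Section 2 grounds it in the experimental manipulation, which the group comparisons also address. Still, the correlation is the only analysis placed under this objective.

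**Conclusion.** The concern holds in conditional form and should be fixed. Followed as written, the causal-role correlation leaves its false-positive rate uncontrolled. At a nominal 5% the rate is:

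- about 5-8% with activation-change ICC 0-0.1 and no strong trend;
- 7-9% at ICC 0.2-0.3, without trend;
- 15-17% at ICC 0.5, without trend;
- about 27% at ICC 0.7, without trend;
- about 20-34% with a shared 1 SD trend, for ICC 0 to 0.7.

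These figures assume the pooled reading, a Pearson test and the 5% level carried over from the ANCOVAs. The ICCs and the trend are not in the documents.

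Two parts need no such assumption: the stated target (symptoms) and the variable used (MSIT performance) do not match, and Section 8 specifies no group comparison of ACC regulation during feedback or transfer blocks. This is a secondary analysis in a 20-patient exploratory trial and can be repaired before analysis, so it is a should-fix and not a threat to the trial as a whole.

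**What to change.** Amend Section 8, using the data already planned:

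1. Replace the pooled correlation by a mixed model of next-session MSIT score on patient-mean-centred change in dorsal ACC activation. Include session as a categorical term, group, group x session, group x ACC change and a patient random intercept. Add a sensitivity analysis with patient-specific slopes, because patient and session terms alone do not fully hold the level if slopes differ between patients.
2. State that the activation measure comes from the dorsal ACC in both arms.
3. Call the outcome of this analysis cognitive interference. For symptoms, relate each patient's mean ACC regulation to the post-training ADHD score adjusted for baseline, one record per patient, and report it as an association.
4. As a separate point, add a group x session comparison of dorsal ACC activation during feedback or transfer blocks, so that the first goal in Section 2 is tested.

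The cost is wording and slightly more analysis work. P-values will be less favourable than those from the pooled correlation, and the symptom analysis will rest on only 20 records.
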